### Ethical approval and trial-registration

The MSCIMS trial was granted ethical approval following Research Ethics Committee review (07/Q0108/104) and is registered with the NIH clinical trials database (NCT00395200).

## Results

### Recruitment & retention of participants

Ninety-eight subjects were screened between November 2007 and June 2009, with fourteen (14.3%) meeting all eligibility criteria (Figure 1). Three subjects declined participation following detailed discussions and one participant withdrew consent shortly after recruitment for personal reasons.

**Figure 1 F1:**
[figure not shown]
**Recruitment and retention to treatment cohort**.

### MSC culture results

MSCs were successfully isolated and cultured to the target dose from all bone marrow aspirates (mean total cultured dose = 2.0 ×10^6 ^cells / kg; range 1.1 to 3.7 ×10^6 ^cells / kg). Mean culture duration was 24 days (range 20 to 30 days) with a mean cell-doubling time of 1.5 days (range 1.3 to 2.0 days). All MSC cultures were characterised to ISCT definition criteria, had normal karyotype by array-CGH, and no evidence of pathogenic contamination.

### Baseline assessment results

#### (i) Patient-based measures

Baseline results for patient-based outcomes in the treatment group are shown in table 3 (table 3). Mean EDSS was 6.1 (range 5.5 to 6.5). All patients had higher MS Functional Composite (MSFC) disability scores than the National Multiple Sclerosis Society (NMSS) Task Force reference population mean (Mean MSFC z-score -1.5; range -0.4 to -5.4). Eight patients had Beck's Depression Inventory-II scores in the range for minimal depression (0 - 13), one patient scored in the range for mild depression (14 - 19), and one patient scored in the range for moderate depression (20 - 28).

**Table 3 T3:** Patient-based measures in treatment group

	Mean	SD	Range
**BDI-II score**	8.2	7.6	1 - 25
**MSIS-29 Physical score**	66.3	9.5	51 - 80
**MSIS Psychological score**	20.7	5.2	11 - 27
			
**EDSS**	6.1	0.3	5.5 - 6.5
**ACE-R score**	92.4	5.9	85 - 100
			
**MSFC (total) z-score**	-1.5	1.4	-5.4 - -0.4
*MSFC (arm) z-score*	-1.5	0.6	-2.7 - -0.7
*MSFC (leg) z-score*	-2.0	4.1	-13.7 - -0.3
*MSFC (cognitive) z-score*	-0.9	1.1	-2.1 - 1.2
			
**Normalised brain volume (ml)**	1486	75	1361 - 1586
**T_2 _lesion volume (cm^3^)**	40.5	30.1	3.4 - 99.5
**T_1 _lesion volume (cm^3^)**	10.2	9.5	0.6 - 31.3
			

BDI-II = Beck's Depression Inventory II; MSIS-29 = Multiple Sclerosis Impact Score (29 - item); EDSS = expanded Kurtzke disability status scale; ACE-R = Addenbrooke's Cognitive Examination (Revised)

#### (ii) Optic nerve-based measures

Baseline results for optic nerve-based outcomes are shown in table 4. Visual evoked potentials were abnormal in all treatment arm participants (18 of 20 eyes showing changes consistent with demyelination). Retinal nerve fibre layer thickness was reduced by 15.3% in patients' eyes with a previous history of optic neuritis or Unthoff's phenomenon (clinically affected) compared to clinically unaffected eyes (Absolute values: 72.4 μm [SD 12.9 μm] *vs*. 85.5 μm [SD 10.2 μm]; p = 0.0399). Full-field VER latency was prolonged by 18.7% in clinically affected eyes compared to clinically unaffected eyes (Absolute values: 136.3 ms [SD 15.2 ms] *vs*. 114.8 ms [SD 7.1 ms]; p = 0.0045).

**Table 4 T4:** Optic nerve-based measures in treatment group

	Clinically Affected (mean, SD)	Clinically Unaffected (mean, SD)	p
**Number of optic nerves (n)**	14	6	
			
**LogMAR**	0.15 (0.20)	0.15 (0.17)	0.9640
**Sloan 25%**	0.31 (0.26)	0.30 (0.20)	0.9746
**Sloan 5%**	0.66 (0.35)	0.53 (0.18)	0.4282
**Sloan 1.25%**	1.0 (0.46)	0.75 (0.15)	0.1544
			
**FM-100 Square-Root Total Error Score**	16.0 (4.4)	13.5 (2.8)	0.2188
**Visual field Mean Deviance**	-4.28 (2.04)	-3.04 (2.06)	0.2267
			
**RNFL average thickness (microns)**	72.4 (12.9)	85.5 (10.2)	0.0399
**Macular volume (mm^3^)**	6.1 (0.5)	6.6 (0.3)	0.0624
			
**Full field VER latency (milliseconds)**	136.3 (15.2)	114.8 (7.1)	0.0045
**Full-field VER amplitude (microvolts)**	4.8 (1.9)	4.5 (2.3)	0.7669
			
**Optic nerve area (mm^2^)**	8.1 (1.3)	8.9 (1.1)	0.1961
**Optic nerve MTR (pu)**	28.4 (2.9)	31.3 (2.3)	0.0515
			
**Optic nerve DTI Mean Diffusivity (×10^-3 ^mm^2^/s)**	1.17 (0.29)	1.25 (0.26)	0.5415
**Optic nerve DTI Fractional Anisotropy (×10^3^)**	298.2 (91.2)	353.3 (88.6)	0.2282
**Optic nerve DTI Radial Diffusivity (×10^-3 ^mm^2^/s)**	0.99 (0.26)	1.03 (0.24)	0.7004
**Optic nerve DTI Axial Diffusivity (×10^-3 ^mm^2^/s)**	1.53 (0.42)	1.70 (0.35)	0.4012
			

FM-100 = Farnsworth-Munsell 100-Hue test; RNFL = Retinal Nerve Fibre Layer; VER = Visual Evoked Response; DTI = Diffusion Tensor Imaging.

#### (iii) Comparative performance between patients and controls

Normalised brain volume was reduced by 11.1% in patients compared to controls (Absolute values: 1486 cm^3 ^[SD 75 cm^3^] *vs*. 1671 cm^3 ^[SD 53 cm^3^]; p < 0.00005). There were no significant differences in brain imaging MTR measures between controls and patients although there was a trend to higher MTR values in controls. Whole brain (mean) MTR was reduced by 5.3% in patients (Absolute values: 44.52 pu [SD 6.56 pu] *vs*. 47.02 pu [SD 4.48 pu]; p = 0.3976). Grey matter (mean) MTR was reduced by 7.2% in patients (Absolute values: 35.20 pu [SD 7.34 pu] *vs*. 37.95 pu [SD 5.14 pu]; p = 0.4061). White matter (mean) MTR was reduced by 4.6% in patients (Absolute values: 46.37 pu [SD 6.92 pu] *vs*. 48.63 pu [SD 4.49 pu]; p = 0.4623).

Optic nerve-based measures showed significant differences between patients and controls in measures of RNFL average thickness and optic nerve area, and in DTI measures of mean diffusivity, fractional anisotropy and radial diffusivity (table 5).

**Table 5 T5:** Optic nerve-based measures in patients and controls

	PATIENTS		CONTROLS	
			
	Clinically Affected (mean, SD)	Clinically Unaffected (mean, SD)	(mean, SD)	p*
**Number of optic nerves (n)**	14	6	16	-
				
**RNFL average thickness (microns)**	72.4 (12.9)	85.5 (10.2)	101.6 (12.1)	0.0093
**Macular volume (mm^3^)**	6.1 (0.5)	6.6 (0.3)	6.9 (0.4)	0.1211
				
**Optic nerve area (mm^2^)**	8.1 (1.3)	8.9 (1.1)	10.3 (0.8)	0.0123
**Optic nerve MTR (pu)**	28.4 (2.9)	31.3 (2.3)	32.9 (3.4)	0.2700
				
**Optic nerve DTI Mean Diffusivity (×10^-3 ^mm^2^/s)**	1.17 (0.29)	1.25 (0.26)	0.97 (0.13)	0.0145
**Optic nerve DTI Fractional Anisotropy (×10^3^)**	298.2 (91.2)	353.3 (88.6)	530.6 (99.7)	0.0004
**Optic nerve DTI Radial Diffusivity (×10^-3 ^mm^2^/s)**	0.99 (0.26)	1.03 (0.24)	0.67 (0.13)	0.0007
**Optic nerve DTI Axial Diffusivity (×10^-3 ^mm^2^/s)**	1.53 (0.42)	1.70 (0.35)	1.58 (0.23)	0.4809
				

RNFL = Retinal Nerve Fibre Layer; VER = Visual Evoked Response; DTI = Diffusion Tensor Imaging. * Significance test for control *vs*. patient by 2-way ANOVA controlling for optic nerve status in patient group (clinically affected/unaffected)

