### Blinding and data analysis

Optic nerve area, optic nerve MTR, and optic nerve DTI based outcomes were assessed by observers blind to participant status (pre/post-treatment). Lesional analysis was performed shortly after image acquisition at each visit. Brain volume, brain MTR, and fMRI analyses were performed using automated methods with minimal manual corrections; blinding was not therefore performed. Group comparisons for baseline outcomes were performed by Student's t-test. Following trial completion, safety data will be analysed to assess whether the post-intervention period is associated with an increase in adverse events; and efficacy data will be analysed to assess whether the post-intervention period is associated with a difference in pre-defined outcomes. No interim analyses are planned.

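### Table 5 labels its p-values as control versus patient, but they compare the 16 control eyes with only the 6 clinically unaffected patient eyes

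*Protocol article*

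**What the plan says.** Table 5 (Results, Baseline assessment results, part iii) gives means and SDs for 14 clinically affected patient eyes, 6 clinically unaffected patient eyes and 16 control eyes, with one p column. The footnote describes that column as a significance test of control versus patient "by 2-way ANOVA controlling for optic nerve status in patient group (clinically affected/unaffected".

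The text above the table reads: "Optic nerve-based measures showed significant differences between patients and controls in measures of RNFL average thickness and optic nerve area". It then adds DTI mean diffusivity (MD), fractional anisotropy (FA) and radial diffusivity (RD). Macular volume, optic nerve MTR and axial diffusivity (AD) are not in the list.

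Part ii of the same section reports the visual evoked potentials of the treatment arm as "18 of 20 eyes showing changes consistent with demyelination". In Methods, Blinding and data analysis, the only test named is in the sentence "Group comparisons for baseline outcomes were performed by Student's t-test".

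**The concern.** A two-way layout of group (patient, control) by eye status (affected, unaffected) has an empty cell here, because no control eye is clinically affected. With both terms in the model, the group coefficient is the difference between patients and controls at the status they share, which is unaffected. The 14 affected eyes are 70% of the patient eyes, yet they do not contribute to the estimated difference.

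The p column would then answer a narrower question than its label states, and the summary sentence would draw its list from that narrower question. Someone using Table 5 to judge which anterior visual pathway measures separate patients with MS from healthy controls would pass over macular volume and optic nerve MTR. The 6 unaffected eyes are also an odd stand-in for patients as a whole. Only 2 of the 20 patient eyes lacked changes suggesting demyelination, so at least 6 − 2 = 4 of these 6 eyes had them.

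**Working it through.** **Inputs**, all from Table 5 (affected n = 14 / unaffected n = 6 / control n = 16; mean (SD); printed p):

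- RNFL: "72.4 (12.9) 85.5 (10.2) 101.6 (12.1) 0.0093"
- Macular volume: "6.1 (0.5) 6.6 (0.3) 6.9 (0.4) 0.1211"
- Optic nerve area: "8.1 (1.3) 8.9 (1.1) 10.3 (0.8) 0.0123"
- MTR: 28.4 (2.9) / 31.3 (2.3) / 32.9 (3.4); 0.2700
- MD: 1.17 (0.29) / 1.25 (0.26) / 0.97 (0.13); 0.0145
- FA: 298.2 (91.2) / 353.3 (88.6) / 530.6 (99.7); 0.0004
- RD: 0.99 (0.26) / 1.03 (0.24) / 0.67 (0.13); 0.0007
- AD: 1.53 (0.42) / 1.70 (0.35) / 1.58 (0.23); 0.4809

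**Step 1: reproduce the printed p-values.** In the three-cell model,

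MSE = [13·SD(aff)² + 5·SD(unaff)² + 15·SD(ctl)²] / 33

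t = [mean(ctl) − mean(unaff)] / √[MSE·(1/6 + 1/16)], on 33 df, two-sided.

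Example, RNFL: MSE = 4879.68/33 = 147.87; SE = √(147.87 × 0.2292) = 5.82; t = (101.6 − 85.5)/5.82 = 2.77; p = 0.0092.

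The range shows the effect of varying each input within its printed rounding.

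| Measure | Recomputed p (range) | Printed p |
|---|---|---|
| RNFL | 0.0092 (0.0087–0.0098) | 0.0093 |
| Macular volume | 0.154 (0.044–0.362) | 0.1211 |
| Area | 0.0099 (0.0047–0.0191) | 0.0123 |
| MTR | 0.283 (0.252–0.317) | 0.2700 |
| MD | 0.0142 (0.0104–0.0184) | 0.0145 |
| FA | 0.00044 (0.00043–0.00044) | 0.0004 |
| RD | 0.00096 (0.00064–0.00143) | 0.0007 |
| AD | 0.459 (0.420–0.498) | 0.4809 |

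All eight agree within rounding. The alternatives do not fit:

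- All 20 patient eyes against controls: RNFL about 0.000001, MTR 0.0017, AD 0.99.
- Equal-weight average of the two patient groups against controls: RNFL 0.00001, MTR 0.0074, AD 0.77.
- Plain t-test of 6 against 16 eyes: area 0.0035, MD 0.0028, AD 0.356.

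**Step 2: compare all patient eyes with controls.** Patient mean = 0.7·mean(aff) + 0.3·mean(unaff). The patient SD combines within-group and between-group variation over 19 df.

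- Macular volume: mean 0.7 × 6.1 + 0.3 × 6.6 = 6.25, SD 0.50. Pooled SD with controls 0.459; SE = 0.459 × √(1/20 + 1/16) = 0.154; t = 0.65/0.154 = 4.23 on 34 df; p = 0.0002 (rounding range 0.00001–0.0014).
- MTR: mean 0.7 × 28.4 + 0.3 × 31.3 = 29.27, SD 3.00. Pooled SD 3.18; SE = 1.07; t = 3.63/1.07 = 3.40; p = 0.0017 (0.0013–0.0023).

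**Step 3: allow for two eyes per person.** The inter-eye correlation ρ is not given. Scale the per-person variance by (1 + ρ)/2, with 10 against 8 participants and 16 df.

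| Measure | ρ = 0.5 | ρ = 1 |
|---|---|---|
| Macular volume | 0.003 | 0.009 (rounding range 0.002–0.026) |
| MTR | 0.013 | 0.029 (0.025–0.033) |
| MD | 0.028 | 0.052 |

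At ρ = 1, RNFL (0.0008), area (0.002), FA (0.0002) and RD (0.004) stay below 0.05, and AD stays far above it.

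**Step 4: change the weighting.** Weight the two patient groups equally, with SE = √[MSE·(0.25/14 + 0.25/6 + 1/16)].

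- Eye level (33 df): macular volume p = 0.0009; MTR p = 0.0074.
- ρ = 1 (SE multiplied by √2, 16 df): macular volume t = 0.55/0.212 = 2.59, p about 0.02; MTR t = 3.05/1.51 = 2.02, p about 0.06.

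**The case against.** The footnote does disclose that status is controlled for, and the table prints all three groups, so a careful reader can see that affected eyes lie further from controls. An adjusted contrast is also a reasonable one to report. Patients were selected for optic nerve involvement (Table 1), so part of any unadjusted difference is built in, and the 14:6 mix is an accident of enrolment. This supports keeping the contrast under its proper name. It does not support calling it control versus patient.

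A reader might infer that the article declares macular volume and optic nerve MTR not to differ. It does not. Non-difference is implied by omission and by the printed p-values; the explicit statement of no significant differences concerns brain MTR.

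A reader might also infer that the choice of trial outcomes or the efficacy analysis is undermined. The documents do not support that. The article sets out to report design and baseline characteristics. Controls were recruited to gauge inter-session variability. Both measures are already listed as outcomes, and nothing shows Table 5 being used to select, drop or power one.

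The mismatch with the t-test named in Methods is not a fault in itself, since a table footnote may name its own test. It does mean that no other text explains the contrast.

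**Conclusion.** The point holds as a moderate error in the reported baseline results. Every p-value in Table 5 is misdescribed, and the summary sentence rests on a contrast that excludes 14 of the 20 patient eyes from the difference.

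The practical consequence is two omissions. Macular volume is the firm one: it stays below 0.05 under every weighting and correlation tried. MTR is less robust and depends on the weighting if the eyes are perfectly correlated. In the other direction, MD slips to about 0.05 only at that same extreme; the other four listed measures stand.

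These conclusions assume a two-sided 0.05 level, which the article does not state, and inter-eye correlations up to 1, which it does not report. They are computed from rounded summary statistics. The safety objective and the planned comparison of the periods before and after treatment are unaffected.

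**What to change.** The minimum is to relabel the p column and footnote as controls versus clinically unaffected patient eyes, and to reword the summary sentence so that it claims only that.

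The better option is to replace the column. For each measure, fit one model with a three-level eye group (control, clinically unaffected, clinically affected) and a random participant effect. Report the patient-versus-control contrast with its weighting stated, show affected versus control and unaffected versus control separately, and rewrite the list of differing measures to match.

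The cost is eight models on data already in hand, one table column, one footnote and one sentence.

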## Discussion

The MSCIMS trial aims to establish the safety and feasibility of autologous intravenous mesenchymal stem cell therapy in multiple sclerosis. In addition, it provides an opportunity to advance trial methodology for the assessment of putative neuroprotective agents in MS, and inform the design of subsequent trials to test potential efficacy. Two aspects of design are of particular note due to their potential for wider application. First, a pre-test : post-test design was chosen in order to maximise the opportunity to inform on potential efficacy in a small cohort with an unknown effect size. Given that *intra*-individual variance in the rate of disease progression in MS measured clinically or radiologically is less than *inter*-individual variance,[23-25] the advantage of using a pre-test : post-test design is to increase the effect size between comparator groups and therefore increase statistical power by 40-80% [26]. Second, differences between patients in terms of disease pathology, course, and phenotype represent a significant challenge in MS clinical trials, necessitating the use of multidimensional outcome scales that are insensitive to small effect sizes, and serving to inflate the sample size required to achieve adequate power [27]. The MSCIMS trial uses complementary eligibility criteria and tailored outcome measures to study therapeutic response in participants who have deficits in the anterior visual pathway *as a model of wider disease processes*. This "sentinel lesion" approach forms a novel methodology for neuroprotective trials in MS and the MSCIMS trial assesses proof-of principle for its utility.

In order to establish the safety profile of the intervention, selection and timing of appropriate outcomes has been guided by the published literature on intravenous MSC therapy. Immediate adverse events consistent with type I hypersensitivity (pruritis, rash, fever) are reported in approximately 10% of subjects following intravenous administration of autologous or allogeneic MSCs. Intensive monitoring for evidence of allergic reactions is therefore scheduled around the time of infusion. Medium and long-term adverse event risks are less well characterised from the published literature, but include a theoretical risk of increased susceptibility to infection and neoplasia. Weekly assessment (×4) following infusion is designed to specifically screen for the former, and long term monitoring the latter. Given that the majority of the published cohort of patients who have undergone treatment with intravenous MSCs have been treated in the context of haematological malignancy, follow up of the MSCIMS trial cohort offers a unique opportunity to define long-term safety in a group with longer life-expectancy and a lower background rate of disease complications.

The treatment cohort in this trial is typical of patients with established progressive MS in terms of disability levels at recruitment and low relapse frequency (two participants in the treatment group experienced episodic clinical disease activity). While this group is appropriate for safety-assessment of novel therapies, it may be sub-optimal for assessment of therapeutic efficacy in later phase trials. Given that the assessment of neuroprotection requires efficacy endpoints based on demonstrating a reduction in the rate of neurodegeneration, a group showing dynamic (active) progression may be preferable in order to avoid type II error. Alternatively, in cohorts with more modest rates of neurodegeneration/progression, longer follow up may be required to achieve sufficient power. Two recent reports have described the use of intrathecally delivered autologous MSCs in MS without adverse events or significant change on global clinical outcomes [28,29]. However, this may reflect the significant challenge of demonstrating neuroprotection with global outcomes in small early phase clinical trials and a disease characterised by clinical and pathological heterogeneity. Against this background, we propose that an approach targeting a clinically articulate system with a range of tailored outcomes, as illustrated by the MSCIMS trial methodology, offers increased sensitivity to demonstrate structural and functional change in response to a putative neuroprotective intervention.

## Conclusions

The MSCIMS trial represents a novel approach for evaluating neuroprotective therapies in MS. It will establish the initial safety profile and feasibility of the intervention, allow informed design of subsequent studies to address efficacy, and test the utility of a novel methodology for neuroprotective trials in MS with potential for wider future application.

## Abbreviations

**ACE-R: **Addenbrooke's Cognitive Examination (Revised); **AD: **Axial diffusivity; **APTT: **Activated partial thromboplastin time; **BAC: **Bacterial artificial chromosome; **BDI-II: **Beck's depression inventory (II); **BOLD: **Blood oxygen level dependent; **CMV: **Cytomegalovirus; **DTI: **Diffusion tensor imaging; **EBMT: **European Group for Blood and Marrow Transplantation; **EDSS: **Expanded (Kurtzke) disability status score; **EDTA: **Ethylenediaminetetraacetic acid; **FA: **Fractional anisotropy; **fMRI: **Functional MRI; **FOV: **Field of view; **GM: **Grey matter; **ISCT: **International Society of Cellular Therapy; **JACIE: **Joint accreditation committee for ISCT-EBMT; **HIV: **Human immunodeficiency virus; **HTLV: **Human T-lymphotrophic virus; **MD: **Mean diffusivity; **MDEFT: **Modified driven equilibrium fourier transform; **MRI: **Magnetic resonance imaging; **MS: **Multiple sclerosis; **MSC: **Mesenchymal Stem Cell / Multipotent mesenchymal stromal cell; **MSCIMS: **The mesenchymal stem cells in multiple sclerosis trial; **MSFC: **Multiple sclerosis functional composite score; **MSIS-29: **Multiple sclerosis impact scale (29-item); **MTR: **Magnetisation transfer ratio; **MV: **Macular volume; **NAGM: **Normal appearing grey matter; **NAWM: **Normal appearing white matter; **OCT: **Optical coherence tomography; **PD: **Proton density; **PT: **Prothrombin time; **RD: **Radial diffusivity; **RR-MS: **Relapsing remitting multiple sclerosis; **RNFL: **Retinal nerve fibre layer; **SIENA: **Structural image evaluation using normalisation of atrophy; **SPM: **Statistical parametric mapping; **SP-MS: **Secondary progressive multiple sclerosis; **sTE fFLAIR: **Fat saturated short echo fast fluid attenuated inversion recovery; **VER: **Visual evoked response; **WB: **Whole brain; **WM: **White matter
